
## Methods

### Study aims

The primary aim of the BiPOWR trial is to prospectively describe and compare efficacy (coronal and sagittal curve maintenance) and –safety (occurrence of Serious Adverse Events; SAEs) of two innovative implant systems in neuromuscular EOS patients. Due to the relatively short follow-up of participants (1 year), with intermediate instead of final outcomes, the study is regarded as a limited-efficacy and -safety study [21]. A secondary aim is to describe and compare spinal- and implant growth, peri-operative parameters and Health-Related Quality of Life (HRQoL).

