**Outcomes**								
Main coronal Cobb angle	X			X	X	X	X	X
Serious Adverse Events			X	X	X	X	X	X
Implant length				X	X	X	X	X
EOSQ-24 questionnaire	X			X	X	X	X	X

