### Outcomes

The primary outcomes include coronal Cobb angle – measured on radiographs – and occurrence of SAEs (defined as unplanned medical events which (could) result in permanent disability/damage, or which requires (lengthening of) hospitalization, a re-operation, or inpatient medical managing). SAEs will be categorized as either device/surgery related (e.g. rod fracture, post-operative neurological deficit), or as disease-related (e.g. pneumonia, pain) according to a previously created complication classification system for use in EOS treatment [24]. In addition to SAEs, complications that do not meet the criteria for an SAE, but which are device/surgery related (e.g. superficial infections, proximal junctional kyphosis) will also be recorded.

Secondary radiographic measurements include parameters such as T1-T12, T1-S1 and instrumented height, T5-T12 kyphosis, L1-S1 lordosis, and pelvic obliquity. In addition, implant length will be calculated at each timepoint for both groups (SDS: Spring length, OWSER: Notched rod length) so that implant growth velocity over time can be graphed and calculated. The number of outpatient axial traction events of OWSER patients, if these are performed, will also be reported. All radiographic measurements will be performed by a trained assessor. To ensure data quality, radiographic measurements are performed semi-automatically in Surgimap v2.3.2.1 software (Nemaris, New York, USA), after which all measurements are audited by the assessor. At the end of the data collection phase, all radiographic measurements are re-assessed by a second trained assessor who is blinded to the first assessors’ measurements. Measurements are compared and disputed measurements are discussed until consensus is reached. If differences are believed to be caused by random measurement variation, the arithmetic mean of both assessors’ measurement is taken.

HRQoL will be measured with the validated Dutch version of the EOSQ-24 which consists of 24 questions in 10 domains, from which a domain- and total score is calculated [25, 26]. All outcome parameters are measured pre-operatively, immediately post-operatively, and at 1, 3, 6, and 12 months follow-up.

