### Sample size calculation and statistical methods

The sample size calculation is based on potential differences between groups in maintenance of the coronal curve between the post-operative situation and 1-year follow-up. A difference in Cobb angle ≥ 5˚ is considered clinically relevant and can be reliably measured [27]. In our previous MCGR cohort studies, we found a change in Cobb angle between post-operatively and 1 year follow-up of 1˚ (SD 5.1˚) [28]. To determine differences in curve maintenance between groups ≥ 5˚ with a power (1-β) of 0.8, α = 0.05, and SD = 5.1˚, we calculated a sample size of n = 28, with a repeated measures ANOVA between factors design (comparing 2 timepoints). With an allocation ratio of 1:1, this means that 14 patients have to be included in each experimental group.

If all assumptions for performing repeated measures ANOVA are met, both systems will be compared with respect to coronal curve maintenance; age and sex will be included as covariates. For the other continuous variables, repeated measures ANOVA will be used, with the same covariates, but including all evaluated time points. If the assumptions for performing repeated measures ANOVA are not met (e.g. due to missing data), repeated measurement multilevel modelling will instead be performed, with patient, age, sex and treatment group as level 2 variables, and follow-up time as a level 1 variable.

A Kaplan–Meier survival analysis will be performed comparing both groups. The survival curves showing SAE-free survival of both groups will be statistically compared with the Log-Rank test. Analysis of EOSQ-24 scores will be performed using repeated measures ANOVA. In case there are missing EOSQ-24 item scores or questionnaires, multiple imputation with parcel summary scores will be performed using a previously published statistical method [29]. For all statistical tests, statistical significance will be set at *p* < 0.05. All statistical analyses will be performed in IBM SPSS statistics v.26.0.0.1 (Chicago, USA).

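### For T1-T12 and T1-S1 height, a repeated measures ANOVA that includes the pre-operative film mixes height gained at surgery with spinal growth afterwards

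*Protocol article*

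**What the plan says.** Study aims (protocol article): "A secondary aim is to describe and compare spinal- and implant growth" between the two implants.

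Outcomes: "Secondary radiographic measurements include parameters such as T1-T12, T1-S1 and instrumented height", and on timing, "All outcome parameters are measured pre-operatively, immediately post-operatively, and at 1, 3, 6, and 12 months follow-up". That is six occasions, one of them before surgery. The SPIRIT table (Table 1) has no row for any height, so the pre-operative height measurement rests on this sentence.

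Sample size calculation and statistical methods: the primary Cobb analysis concerns "maintenance of the coronal curve between the post-operative situation and 1-year follow-up". The next rule covers the rest: "For the other continuous variables, repeated measures ANOVA will be used, with the same covariates, but including all evaluated time points". If the ANOVA assumptions fail, a multilevel model replaces it, with "follow-up time as a level 1 variable". Neither model is given a post-operative starting point, a separate surgical phase or a named contrast for spinal height.

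**The concern.** Spinal growth is what happens after the implant is in place. The step from the pre-operative film to the first post-operative film is height gained by straightening the spine at operation. With six occasions in one time factor, the group-by-time interaction asks whether the two mean profiles differ in shape anywhere, including at that step.

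A different operative gain in the two arms is plausible from the article's own description. One system uses tensioned springs and a three-level pedicle-screw anchor; the other lengthens passively and uses hooks spanning five vertebrae. No figure for operative gain is given.

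Two things are at stake. A significant interaction could be read as a growth difference when only the operation differed. And patient-to-patient variation in operative gain enters the error term, so a real growth difference is harder to detect. The article pins down the time window here; it does not leave it open. The primary outcome gets a post-operative start, and the other outcomes explicitly get a wider one.

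**Working it through.** **The plan's own figure.** The only sample-size figure is N = 28 for the Cobb angle. With f = (5/5.1)/2 = 0.490, two time points and the between-factors formula λ = f²·N·2/(1+ρ), power is 0.791 at N = 26 and 0.822 at N = 28 if ρ = 0.5. The article does not state ρ; 0.5 is an assumption. So N = 28 reproduces, and nothing below changes it. There is no planning figure for spinal height.

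**Inputs.** From the article: 14 per arm; six occasions (pre-operative, then 0, 1, 3, 6 and 12 months); α = 0.05. Assumed, because the article gives none: SD of operative gain 15 mm (range 10-20), SD of one-year growth 8 mm (range 4-10), reading error SD 4 mm.

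**What the interaction picks up.** Write the between-arm difference profile over the six occasions and sum the squared deviations from its own mean.
- Operative difference d, profile (0, d, d, d, d, d): d² × (1 × 5)/6 = 0.833 d². Over the five post-operative occasions the profile is flat, and the sum is 0.
- Growth difference g, profile g × (0, 0, 1/12, 3/12, 6/12, 1): 0.759 g² over six occasions; 0.647 g² over the five post-operative ones.

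Expected within-patient residual sum of squares per patient, at SDs 15/8/4:
- six occasions: 15² × 0.833 + 8² × 0.759 + 5 × 4² = 187.5 + 48.6 + 80 = 316.1;
- five post-operative occasions: 8² × 0.647 + 4 × 4² = 41.4 + 64 = 105.4.

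So 187.5/316.1 = 59% of the six-occasion residual is variation in operative gain, which says nothing about growth.

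The interaction F ratio is roughly 1 + (n/2) × signal/residual, with n/2 = 7:
- operative difference 10 mm, no growth difference, six occasions: 1 + 7 × 83.3/316.1 = 2.85; post-operative only: 1;
- growth difference 8 mm, no operative difference, six occasions: 1 + 7 × 48.6/316.1 = 2.08; post-operative only: 1 + 7 × 41.4/105.4 = 3.75.

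**Rejection rates by simulation** (Greenhouse-Geisser corrected group-by-time test, no covariates, 4,000 runs per scenario, SDs 15/8/4):

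| True difference between arms | Six occasions | Post-operative only |
|---|---|---|
| None | 5% | 5% |
| Operative gain 5 mm | 12% | 4% |
| Operative gain 10 mm | 34% | 4% |
| Operative gain 15 mm | 68% | 5% |
| Operative gain 20 mm | 89% | 4% |
| Growth 8 mm, equal operative gain | 20% | 55% |

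**Range over the assumed SDs** (operative/growth, reading error 4 mm):
- 10/5: a 10 mm operative difference gives 61%; power for 8 mm of growth is 43% with the pre-operative film and 74% without.
- 20/10: 22%; power 12% and 44%.
- 12/4: operative differences of 5, 10 and 15 mm give about 15-18%, 50% and 82-84% over repeated runs, against 4-5% post-operatively.

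**The case against.** The strongest reply is that the article names a model and its occasions, but does not say that the six-level interaction is the growth test. The same model can yield a post-operative to 12-month contrast, and the choice of contrast is detail that a full protocol or analysis plan often holds. The visit-by-visit values would also show where the profiles part. This stands in part. It means that misreading could happen, not that it would. It does not remove the point, because the stated window includes the pre-operative film and a contrast picked after the data are seen is weaker than one named now.

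Second, the size rests on assumed millimetres. That is correct. If operative gain is the same in both arms, there is no false growth signal. The loss of power remains in that case, because it comes from variation in operative gain within arms.

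A reader might also stretch the point further than the documents allow:
- *Implant length.* Table 1 schedules "Implant length" only from one week after surgery, so its evaluated occasions are all post-operative. The sentence that all outcomes are measured pre-operatively is loose for this one, but no analysis error follows.
- *Instrumented height.* Nothing is instrumented before surgery; a pre-operative value is at most a span over planned levels.
- *Kyphosis, lordosis, pelvic obliquity.* No growth aim is stated for these, and a comparison that includes the pre-operative value can be legitimate.
- *Degrees of freedom.* A one-degree-of-freedom contrast is more powerful than an omnibus test with or without the pre-operative film, so that comparison does not measure the harm described here. The figures above compare omnibus with omnibus.

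**Conclusion.** The point holds for T1-T12 and T1-S1 height. As written, the group-by-time test combines surgical gain and later growth, although the stated aim is growth. A 10 mm between-arm difference in operative gain, with identical growth, could make it significant in about 22-61% of trials, against about 5% with post-operative visits only. With equal operative gain, power for a true 8 mm growth difference falls from 44-74% to 12-43% (55% to 20% at the central SDs). All the millimetre values are assumptions, and the simulations leave out the age and sex covariates.

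A reader might infer that the test has an inflated type I error, or that an operative difference will be reported as growth. Neither is supported. The test holds its level when neither gain nor growth differs; the fault lies in what it tests. And no document shows that operative gain differs between arms. The primary outcomes and N = 28 are untouched. This concerns a secondary aim in a study described as limited-efficacy, but the remedy costs almost nothing and should be adopted.

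**What to change.** For T1-T12 and T1-S1 height, state in the analysis plan that:
1. spinal growth starts at the first post-operative film, as curve maintenance already does for the primary outcome;
2. the growth model uses post-operative visits only, with pre-operative height as an optional covariate;
3. the growth test is one named contrast: the between-group difference in change, or in slope, from the first post-operative film to 12 months;
4. surgical gain, from the pre-operative to the first post-operative film, is reported separately;
5. the multilevel fallback uses the same starting point and contrast.

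The other secondary outcomes need no correction on this ground. The cost is a few lines of wording before the data are analysed; no new measurements, visits or patients are needed.

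### The primary question is change in Cobb angle, but the effect named for the sample size compares average Cobb, and no group-by-time term is stated in either model

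*Protocol article*

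**What the plan says.** All of this is in the protocol article, section Sample size calculation and statistical methods.

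- **Target.** The sample size rests on "potential differences between groups in maintenance of the coronal curve between the post-operative situation and 1-year follow-up". The relevant difference is 5 degrees: "To determine differences in curve maintenance between groups ≥ 5" degrees.
- **Variability.** From an earlier MCGR cohort, "we found a change in Cobb angle between post-operatively and 1 year follow-up of 1˚ (SD 5.1" degrees). This is an SD of change.
- **Test behind the sample size.** A repeated measures ANOVA, between-factors design, with two time points, "with a power (1-β) of 0.8" and alpha 0.05, giving 28 patients, 14 per arm.
- **Primary analysis.** Repeated measures ANOVA comparing the systems on coronal curve maintenance, with age and sex as covariates. The term to be tested is not named.
- **Fallback.** A multilevel model replaces the ANOVA when its assumptions fail, missing data being the example given. The article lists what goes into this model by level: "with patient, age, sex and treatment group as level 2 variables, and follow-up time as a level 1 variable".

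The article names no group-by-time interaction, no change score and no adjustment for post-operative Cobb angle.

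**The concern.** Maintenance is a difference between arms in change over time. With two time points, that is the group-by-time contrast, which equals a comparison of change scores. The between-factors effect is a different quantity: the difference between arms in the mean of the two readings.

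The two can lead to opposite conclusions. If the arms start level after surgery and one loses 5 degrees more by 12 months, the between-factors effect sees only half of that. If the arms hold their correction equally well but one achieves more correction at surgery, the between-factors effect can be significant although maintenance does not differ. The second case is not far-fetched: the section Surgical procedure and treatment arms describes different proximal anchors, rod materials and lengthening mechanisms, so correction at surgery may differ.

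The fallback adds to the uncertainty. The Cobb ANOVA is tied to two time points, while the fallback mentions only follow-up time, and Table 1 schedules Cobb before surgery and at five later visits. If all visits were entered with treatment as a main effect, its coefficient would average over them, pre-operative Cobb included. What counts as assumptions not being met is left open apart from the example of missing data.

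**Working it through.** **Inputs from the article:** difference 5 degrees; SD of change 5.1 degrees; power 0.80; alpha 0.05 (taken as two-sided); 14 per arm, N = 28; two time points.

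**Assumptions (not in the article):** the correlation ρ between time points, the per-visit SD s of Cobb, and an 8 degree post-operative difference used as an illustration.

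**1. Reproducing N = 28.** Effect size d = 5/5.1 = 0.980, so f = d/2 = 0.490. For the between-factors effect with m = 2 readings, the noncentrality is λ = f²·N·m / (1 + (m − 1)ρ), with 1 and N − 2 degrees of freedom. With ρ = 0.5:

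- N = 26: λ = 0.2403 × 26 × 2 / 1.5 = 8.33, power 0.791.
- N = 28: λ = 0.2403 × 28 × 2 / 1.5 = 8.97, power 0.822.

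So 28 is the smallest even N that reaches 0.80. For ρ = 0, 0.3, 0.4, 0.6, 0.7, 0.8 and 0.9 the required N is 20, 24, 26, 30, 30, 32 and 34. The within-between interaction formula with the same f and ρ = 0.5 gives 12, not 28. The stated figure therefore fits the design that the article names.

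**2. Power for the stated question.** Two-sided t test on change, d = 0.980, 14 per arm, 26 degrees of freedom, noncentrality 0.980 × √(14/2) = 2.59: power 0.70. Losing 2 degrees of freedom to age and sex leaves it at 0.70. Reaching 0.80 takes 18 per arm, 36 in total.

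**3. What the between-factors test does with a true difference in loss.** Suppose the arms are equal post-operatively and differ by 5 degrees at 12 months. The difference in means is (0 + 5)/2 = 2.5 degrees. Hold the SD of change at 5.1, so that ρ = 1 − 5.1²/(2s²). The SD of a patient's mean is then s·√((1 + ρ)/2).

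**4. What it does when maintenance is equal.** Here the arms differ by the same amount at both time points, so the difference in change is zero.

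| Assumed s | ρ | SD of patient mean | Power, 5 degrees more loss | Rejects, constant 5 degree offset | Rejects, constant 8 degree offset |
|---|---|---|---|---|---|
| 5.1 | 0.50 | 4.42 | 0.30 | 0.82 | 1.00 |
| 10 | 0.87 | 9.67 | 0.10 | 0.26 | 0.56 |
| 15 | 0.94 | 14.78 | 0.07 | 0.14 | 0.28 |

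The test of change has power 0.70 in the loss scenario and rejects in 5% of trials in both offset scenarios, whatever s is. Simulation of 20,000 trials at s = 10 agreed for the loss scenario: 0.106 for the average and 0.705 for change.

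At ρ = 0.5 the SD of change equals the per-visit SD, so the 0.822 in step 1 and the 0.82 in the table are the same number. The power that the article's formula delivers is power to detect a constant 5 degree offset, a situation with no difference in maintenance.

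**The case against.** The strongest reply is that the article never says that treatment enters as a main effect only. Calling treatment a level 2 variable says where it sits in the hierarchy. It is level 2 in any parallel-group trial, with or without a cross-level interaction, and the same list includes patient, which is the grouping unit. A repeated measures ANOVA routinely outputs group by time, and the systems are to be compared on curve maintenance, which points to change. This stands. A reader might infer that the plan excludes the interaction; the document does not support that. It supports the narrower point that the tested term is not fixed, and that the one effect identified, in the sample size, does not measure maintenance. Because N = 28 also results from a one-sided t test on change, the link to the between-factors effect rests on the article's own naming of that design.

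Three further inferences are tempting and do not hold:

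- *That the switch between models lets the primary p-value be chosen.* The switch is written in advance, and its named trigger is missing data, not the treatment result. What remains is that the assumptions are open-ended.
- *That patients with a missing film are dropped.* Missing data is the named reason to leave ANOVA, so for Cobb this largely does not arise.
- *That the EOSQ-24 rule, "In case there are missing EOSQ-24 item scores or questionnaires, multiple imputation with parcel summary scores will be performed", is an error.* It is a secondary outcome handled by a cited method, and using one model for every outcome would be a preference.

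Details such as covariance structure and degrees-of-freedom method may properly sit in an unseen analysis plan. An analysis plan could also name the right contrast, but the published sample size would then be for a different test. The article's own caution that results are only an initial indication does not settle which quantity is tested.

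**Conclusion.** The point holds in this form: the primary efficacy question is a difference in change, the only effect identified for testing is a difference in average Cobb, and neither model is stated with the term that answers the question. Tested as an average, a true 5 degree difference in loss would be detected with probability 0.30 to 0.07, against 0.70 for the test of change. With equal maintenance and an 8 degree post-operative difference, rejection would occur with probability 1.00 to 0.28, against 0.05. These ranges rest on assumed per-visit SDs of 5.1 to 15 degrees, and the 8 degrees is an illustration. The power of 0.70 at 14 per arm needs only the article's 5 degrees, SD of change 5.1 and a two-sided alpha of 0.05. The point should be settled before the analysis, because the choice of term can change the primary conclusion.

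**What to change.** State that the primary efficacy test is the group-by-time contrast, that is, the between-group difference in Cobb change from post-operative to 12 months, reported with its 95% CI. Estimate it from one pre-specified linear mixed model with visit as a categorical factor, group, group by visit, age and sex, accounting for repeated readings within patient. Use this model whether or not data are missing, in place of the rule that depends on assumptions being met.

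Restate the power for this contrast: about 0.70 with 14 per arm (two-sided, SD of change 5.1), instead of 0.80. For reference, 0.80 would need 36 patients.

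The cost is mainly wording, and the model runs in the planned software. There are two downsides: the stated power is less favourable, and with 28 patients the covariance structure must be kept simple.

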## Background

Early Onset Scoliosis (EOS) is a complex three-dimensional deformity of the spine and trunk, which, if left untreated, can result in severe cardiopulmonary compromise or even death [1, 2]. The early onset of the deformity carries with it a high risk of progression, which places importance on early treatment to preserve pulmonary function. This is even more important in patients with neuromuscular diseases such as spinal muscular atrophy or Duchenne muscular dystrophy. In these patients, respiratory muscles that are necessary for normal in- and expiration weaken, which, together with altered chest wall compliance, leads to further respiratory compromise [3, 4]. Whilst a spinal fusion is able to correct the deformity, doing this in the growing spine arrests all further growth, which limits pulmonary function even more [5]. In addition, continued anterior spinal growth after posterior fusion may result in worsening of the curve, a phenomenon known as crankshafting [6]. To circumvent these problems, “growth-friendly” techniques have been developed, which control curve progression while allowing for the spine and trunk to grow. Currently, the most common “growth-friendly” systems are the traditional growing rod (TGR) and the magnetically controlled growing rod (MCGR) [7, 8]. While both systems can control the scoliotic deformity, they have important limitations. For the TGR, the most obvious limitation is the need for repetitive surgical lengthenings (generally every 6 months), which exposes patients to high anesthetic stress at a young age, which may negatively influence neurodevelopment [9]. For the MCGR, lengthenings are non-invasive, but they still require patients to come to the outpatient clinic on a regular basis, more often than in TGR, which imposes a psychological burden on these patients and their parents [10]. In addition, both TGR and MCGR have a high mechanical (i.e. implant-related) complication rate which results in reoperations and diminished length gain [11–16]. The high rate of MCGR dysfunction recently resulted in a temporary suspension of CE certification and the advice to limit MCGR implantation in several countries [17, 18]. To overcome these limitations, two new systems were developed: the Spring Distraction System (SDS), which uses a compressed spring around standard rods to generate distraction, and the One Way Self-Expanding Rod (OWSER, CE-marked as Nemost®; Euros, SAS, La Ciotat, France), which is a one-way sliding rod with split retaining ring system. Both systems are designed to facilitate growth of the spine without interventions, while maintaining curve correction. Previous publications have shown the feasibility of both systems [19, 20]. However, patient populations and surgical strategies were heterogeneous, and the case series design could have led to selection bias. To determine clinical efficacy, identify early mechanical failures, and to generate level 1 evidence for potential differences between the techniques, a single-blinded, prospective randomized trial was considered the ideal strategy.

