### Study design

The BiPOWR trial is a prospective, multicenter, randomized, surgical trial with two parallel groups and a 1:1 allocation ratio. Ethical approval was provided by the Institutional Review Board of the UMC Utrecht (METC 18–179). Following inclusion, patients undergo “growth-friendly” scoliosis surgery with one of two implants, the SDS or the OWSER. Which implant they receive is decided by randomization. Following implantation, the patients are followed until 12 months post-operatively, during which their radiographic- and clinical outcomes will be described and compared. The analysis at 12 months provides a point for interim analysis in the short follow-up, to determine whether one or both implants show short-term technical malfunctions, and to ascertain whether early detectable differences are present in other outcome domains. After the 1 year analysis, both patient cohorts are followed bi-yearly for several more years, until after skeletal maturity, to show efficacy and safety in the long-term. A SPIRIT table showing a detailed follow-up timeline for the first year of follow-up is shown in Table 1.

**Table 1 Tab1:** SPIRIT table

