Although the study will generate high level evidence, there are several limitations to consider. First, this study does not investigate if growth friendly surgery is actually better than continuing conservative treatment, as we only compare surgical treatments. Also, this study does not have a control group, as we compare the SDS with the OWSER, instead of a ‘gold standard’ surgical treatment – i.e., TGRs and/or MCGRs. We chose this design deliberately as we experienced many problems with current standard therapies, from which we conclude that there simply is no accepted ‘gold standard’. In fact, many of our patients are referred to our center because we have the possibility to offer these novel treatments. It would be unethical to ask these patients to be randomized to a treatment of which we know it has serious disadvantages. Obviously, the patient can always choose not to be included in the study and opt for conventional treatments such as TGR or MCGR that we perform regularly.

Second, the primary endpoint is at only one year follow-up. It is possible and likely that complications manifest after this period as is also seen with conventional “growth-friendly” systems [11, 12, 31]. The primary endpoint is, in that sense, a short-term interim analysis to look at early mechanical failures and short-term efficacy, hence the limited-efficacy nature of the study. After completion of the 1-year analysis, both cohorts of patients will be followed for several years until (and even after) skeletal maturity. Only at that point, definitive conclusions regarding efficacy can be drawn. For practical reasons, we did not incorporate the long-term analysis into the primary aim of the BiPOWR trial.

Third, although randomization is obviously a strong method to minimize bias in comparative studies, this carries the risk of being too artificial and not representative [32–34]. One way to mitigate this, is a multicenter approach and sufficient learning curve for both treatments. We recognize, however, that the investigated techniques are new, and only practiced by a selective group of surgeons. This means that the outcomes of the BiPOWR trial should only be used as an initial indication of efficacy and safety. These findings should be confirmed with larger observational studies and registry data.

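### The only stated between-group safety test is time to first SAE of any cause, which dilutes the comparison of implant failures if disease-related SAEs are equally common in both arms

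*Protocol article*

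**What the plan says.** Under Outcomes, the protocol article gives two primary outcomes: "The primary outcomes include coronal Cobb angle – measured on radiographs – and occurrence of SAEs". The SAE definition there covers any unplanned event that needs hospitalization, re-operation or inpatient medical management, whatever its cause. Each event is then classified: "SAEs will be categorized as either device/surgery related (e.g. rod fracture, post-operative neurological deficit), or as disease-related (e.g. pneumonia, pain"). Device/surgery-related complications that fall short of an SAE are recorded as well.

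Under Sample size calculation and statistical methods, the between-group safety analysis is a Kaplan–Meier comparison: "The survival curves showing SAE-free survival of both groups will be statistically compared with the Log-Rank test". It is not limited to a category, and no stated analysis uses the categories. The sample size of 28 is derived from the Cobb angle alone.

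On purpose, the Study design section says the 12-month analysis is there "to determine whether one or both implants show short-term technical malfunctions", and also to look for early differences in other outcome domains. The Discussion calls the primary endpoint a "short-term interim analysis to look at early mechanical failures and short-term efficacy".

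**The concern.** The classification exists, but the one formal safety comparison does not use it. By the article's own definition, SAE-free time ends at the first SAE of any kind.

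Two things follow. First, events that occur at the same rate in both arms pull the hazard ratio towards 1. Second, a child admitted early with pneumonia contributes no later rod fracture or re-operation to the test. Such admissions are foreseeable: the patients are non-ambulant, and the Background says that in neuromuscular disease "respiratory muscles that are necessary for normal in- and expiration weaken".

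At stake is the reading of the result. A non-significant log-rank on all SAEs could be taken as a sign that the two implants are equally safe, when one has more device/surgery-related SAEs than the other.

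**Working it through.** **The plan's own figure.** The plan states no event rate, hazard ratio or power for the safety test, so nothing can be reproduced for it. The N of 28 belongs to the Cobb angle: f = 5/(2 × 5.1) = 0.49, two timepoints, α = 0.05 and an assumed correlation of 0.5 give N = 28 with power 0.82. It says nothing about SAEs.

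**Inputs from the article.** 14 per arm; 12 months of follow-up; "For all statistical tests, statistical significance will be set at" p < 0.05 (sidedness not stated, two-sided used here).

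**Assumptions.** Exponential event times; independent device/surgery-related and disease-related SAEs; no dropout or deaths; the same disease-related risk in both arms. All event risks are assumed.

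**Step 1: hazards.** A 1-year risk p corresponds to a hazard λ = −ln(1 − p). For device/surgery-related risks of 10% and 40%, λ is 0.105 and 0.511, so the hazard ratio is 0.511/0.105 = 4.85.

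**Step 2: pooling.** A common disease-related hazard λd is added to both arms, so the pooled hazard ratio is (0.511 + λd)/(0.105 + λd). At 40% disease-related risk, λd = 0.511 and the ratio is 1.022/0.616 = 1.66.

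**Step 3: power.** Simulated two-sided log-rank, device/surgery-related risk 10% v 40%. Power on device/surgery-related SAEs alone is about 0.46.

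| Disease-related 1-year risk, both arms | Pooled hazard ratio | Power, all SAEs |
|---|---|---|
| 5% | 3.59 | 0.39 |
| 10% | 2.92 | 0.33 |
| 20% | 2.23 | 0.26 |
| 40% | 1.66 | 0.17 |
| 60% | 1.40 | 0.12 |

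With 20% v 60% and a 40% disease-related risk, power falls from about 0.60 to 0.29.

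**Step 4: device events lost to the first-event rule.** In the 10% v 40% scenarios, the share of children with a device/surgery-related SAE in the year who have a disease-related SAE first is about 2%, 5%, 10% and 32% at disease-related risks of 5%, 10%, 20% and 60%.

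**Step 5: can 14 per arm support either test?** Schoenfeld's formula for 80% power is 4 × (1.96 + 0.84)² / (ln HR)². For HR 4.85 it needs 13 events, against 14 × (0.10 + 0.40) = 7 expected. For the pooled HR of 1.66 it needs about 123 events, more than the 28 children in the trial. The device-only test is nearer its target but still short. With 0 of 14 events in an arm, the upper 95% limit for the true risk is 1 − 0.025^(1/14) = 23%.

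**Step 6: the reverse case.** If disease-labelled SAEs also differ by arm, at 10% v 40%, the pooled hazard ratio stays at 4.85 and expected first events rise to 14 × [(1 − 0.9²) + (1 − 0.6²)] = 14 × (0.19 + 0.64) = 11.6. Power on all SAEs is then 0.72 against 0.46 device-only.

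**The case against.** The any-SAE test follows directly from the primary aim under Study aims, which defines safety as the occurrence of SAEs without restriction. Malfunction is one of several purposes given for the 1-year analysis. Both points stand, so the any-SAE analysis should not be dropped.

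A reader might infer that the plan hides implant failures. The article does not support that. Every SAE is classified, lesser device complications are recorded, and a rod fracture after a pneumonia stays in the data and can be described by arm. It is lost only to the one first-event test. A full protocol, which Data Availability says can be requested, may also add analyses by category.

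A reader might also infer that the device/surgery-related endpoint should simply replace the any-SAE endpoint. That is a trade-off. Relatedness is a judgement, the treating physician knows the implant, and patients and caregivers are told after surgery. An any-cause endpoint avoids the attribution step. Nor does the article establish that the implant has no influence on events labelled disease-related: the Background links deformity and chest-wall compliance to respiratory compromise, and the two arms use different proximal anchors. If those events differ by arm, pooling helps (Step 6).

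Finally, the device-only test is underpowered too, and the Discussion already limits the findings to an initial indication of efficacy and safety. That is so. What remains is that the one formal test named does not isolate the implant events that the article says it wants to detect.

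**Conclusion.** The concern holds in a limited form. The stated safety test is poorly matched to one declared purpose of the 1-year analysis, and the planned SAE categories feed no stated comparison. If disease-related SAEs are equally frequent in both arms, the formal comparison is diluted. The loss is modest when they are rare (0.46 to 0.39 at 5%) and severe when they are common (0.46 to 0.12 at 60%). These figures rest on assumed risks, independence and exponential times; the article supplies no rates.

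Three stronger conclusions are not supported: that failures go unrecorded, that the any-SAE endpoint is wrong in itself, and that a device-only test would be adequately powered. At 14 per arm, a non-significant result under either endpoint is not evidence of equal safety.

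**What to change.** Pre-specify time to first device/surgery-related SAE as a key safety comparison alongside any-SAE-free survival. Do not censor it at disease-related SAEs, and treat death as a competing event. For both endpoints, report the 12-month risk per arm and the difference with 95% CI. Give total SAE counts by category and arm, so that second and later events are visible. State that neither test is well powered at N = 28 and that a non-significant result must not be read as equal safety.

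The cost is a few sentences in the analysis plan, since the classification is already planned and no new data are needed. The downside is fewer events in the device/surgery-related comparison, and relatedness that may be judged by staff who know the implant. Keeping the any-SAE analysis guards against the second.
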